#### Blinding

Due to the nature of the intervention it was not possible to blind study personnel or participants after the implementation of the intervention. However, we did conceal the allocation of hamlets to treatment or control status until after the baseline survey in order to minimize opportunities for bias in recruitment of participants and the baseline survey.

#### Monitoring of the intervention

We hired two field workers to conduct monthly site visits to each daycare in the treatment arm. Each month, these study monitors visit all balwadis in random order. During the visit, they verify that the balwadi is operating in the correct location, care is provided by a sanchalika, the balwadi structure is adequate, food is provided, the monitoring systems are operational; the monitors also collect other broad level indicators that the intervention is proceeding as planned.

General records for each balwadi maintained by Seva Mandir will be used to measure the average number of children attending the balwadi each month relative to the total enrollment, and the total number of days the balwadi was operating each month vis-à-vis the number of days it should have been open. The daily operation of each balwadi and attendance of sanchalikas is being assessed using a camera monitoring system. This system, which has been demonstrated to reduce teacher absenteeism [23], requires sanchalikas to take three self-timed photos each day (9:30 am to 10:00 am at opening, a second after 2.5 h, and a third after 6 h). These digital photos are then used to evaluate the number of days when the balwadi was run for at least 6 h, considered a full day of operation. The sanchalika’s payment is based on their attendance. Sanchalikas receive a monthly salary of Rs. 2,275 monthly if they are present for at least 21 days in a month. Each additional full day is incentivized with a bonus of Rs. 400 up to a maximum of Rs. 5,875 per month. Each day missed compared to the 21-day benchmark results in a penalty of Rs. 175 if the balwadi operated for more than ten days in that month and Rs. 50 if the balwadi operated for ten or less days in that month. Additionally, we are measuring how frequently each balwadi is visited by community members; Seva Mandir requires that each balwadi is visited by a delegate from the specific block level every three months, by a delegate from the local zone once a month, and by a member of the village development committee once a month. Records maintained by the sanchalika are being used to measure the materials received at each balwadi, including educational materials, medicines, toys, and utensils.

### Measures

#### Outcome measures

Our primary endpoint is women’s empowerment. We adopted the conceptual approach of Kabeer [8, 9, 24], which incorporates both the personal and political dimensions of empowerment, and developed indicators that captured “women’s sense of self-worth and identity, their willingness to question their own subordinate status, their control over their own lives, and their voice and influence within the family” [8]. We constructed indicators of empowerment, adapted from the Indian National Family Health Survey [25] whenever possible to facilitate comparability, which encompassed four domains: (1) decision making within the family and control over income (e.g., who decides how the money you earn will be used: mainly you, mainly your husband, or you and your husband jointly?); (2) freedom of movement in the public domain (e.g., are you usually permitted to go to the following places—for example, a market within the village—to buy things: on your own, only if someone accompanies you, or not at all?); (3) participation in community and public life (e.g., are you a member of any type of association, group or club which holds regular meetings?); (4) and views and attitudes on critical gender issues (e.g., please tell me if you agree or disagree with each statement: A married woman should be allowed to work outside the home if she wants to). We plan to test the reliability of empowerment measures during the second survey wave.

We will also measure the primary mechanisms hypothesized to link access to daycare to women’s empowerment, including time use, economic opportunity, economic status, and mental health and well-being.

Use of time was measured using a structured questionnaire, adapted from a study by Beaman et al. (2012) [26], that asked respondents whether they spent any time in the past 24 h on specific activities (e.g., gathering fuel or firewood), how much time they spent on each activity, and whether this amount reflected the usual amount of time spent on the activity. The questionnaire also asks whether respondents were paid in cash or in-kind for the activities they engaged in.

We asked about employment experiences, including whether respondents work, their occupation, the type of work, the quantity of work, whether they are paid for their work in cash or in-kind, and what they do with their children while working. Respondents reported the household income received in the past 12 months from various categories (e.g., agricultural income, business income, rents, remittances, government payments). Household wealth is measured using a series of questions about ownership of specific assets (e.g., telephone, bicycle, radio), environmental conditions (e.g., type of water source, sanitation facilities), and housing characteristics, (e.g., number of rooms, materials used for housing construction). Additionally, respondents are asked about savings accounts held by household members, including for each account the type of account, its purpose, the total value, and whether the respondent can use the account to make purchases.

Symptoms of common mental disorders (CMD) are being assessed using the 12-item General Health Questionnaire (GHQ-12) developed by Goldberg [27]. The GHQ-12 produces results that are similar to the longer version of the GHQ and has been found to be a valid screening instrument for CMD in diverse settings [28]. To the best of our knowledge, validation studies have not been conducted among women living in Rajasthan. However, the GHQ-12 demonstrated high sensitivity and specificity in a validation study conducted in Goa, India using a cutoff score of 5/6 [29], a sample of primary care patients in Tamil Nadu using a cutoff score of 2/3 [30], and a sample of ethnic Indian women living in the United Kingdom using a cutoff score of 2/3 [31]. We used the Hindi version of the GHQ-12 translated by Gautam et al. [32].

We asked mothers about the health of their children under the age of six. We asked about their child’s immunization coverage, including Bacillus Calmette-Guérin (BCG), Diptheria-Tetanus-Pertussis (DTP), hepatitis, measles, and polio vaccines. We also asked about the occurrence of specific symptoms over the past month, including fever, persistent cough, diarrhea, broken bones, cuts, or burns. Additionally, we measured child length/height and weight using standardized techniques and this information will be used to derive children’s length/height-for-age, weight-for-age, weight-for-length/height, and body mass index (BMI)-for-age using the World Health Organization Child Growth Standards [33].

#### Other covariates

Other covariates included socio-demographic characteristics, including respondent’s age, educational attainment, religion, caste, and marital status. We asked the respondent to report the following information for all children in the household who were less than eighteen years of age: literacy, enrollment in school, time spent in school in the prior year, highest level of education completed. For children not enrolled in school we asked about why they were not in school and their main occupation. Additionally, we asked about the husband of married respondents, including their age, educational attainment, and occupation.

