**Methods:**

This three-year study takes place in rural communities from five blocks in the Udaipur District of rural Rajasthan. The intervention is the introduction of a full-time, affordable, community-based daycare program. At baseline, 3177 mothers with age eligible children living in 160 village hamlets were surveyed. After the baseline, these hamlets were randomized to the intervention or control groups and respondents will be interviewed on two more occasions. Primary social and economic outcomes include women’s economic status and economic opportunity, women’s empowerment, and children’s educational attainment. Primary health outcomes include women’s mental health, as well as children’s nutritional status.

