## Background

In low- and middle-income countries (LMICs), access to affordable daycare services, defined as “any type of institutional out-of-home care for children younger than five years of age” [1], is limited. India, the setting for our trial, lacks a cohesive system of reliable and affordable daycare services. Recent government efforts, including the expansion of financial assistance for crèches (nurseries where young children are cared for during the workday) in 2005–2006 under the auspices of the Rajiv Gandhi National Crèche Scheme, remain inadequate [2]. A parallel program, the Integrated Child Development Scheme (ICDS), provides meals to children through local facilities called anganwadis, and expansion of the ICDS into a daycare program has been proposed. However, anganwadis reach only about one of every six children and are marked by insufficient hours of operation, poorly trained workers, chronic staff absenteeism, and substandard facilities [3]. It is unclear how existing programs can be adapted to satisfy the demand for full-day childcare.

Women are often charged with the dual responsibilities of child rearing and time-intensive domestic work [3]. Limited access to daycare represents a potential barrier to paid employment, whether in the formal or informal labor market [4, 5]. Women who do enter the labor market by taking up paid employment often retain responsibilities for unpaid domestic work and childcare, forcing them to bring children to work, leave them home unattended, or entrust their care to older siblings [3]. The demand of caring for younger siblings is a key explanation for why adolescent girls, on average, dropout from school before boys [5]; this reduces the economic opportunities available to women directly by limiting their educational achievement and literacy and indirectly by hastening marriage and the time to first childbirth [6, 7].

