	Total sample			Control hamlets			Tread hamlets		
	No.	Mean	SD	No.	Mean	SD	No.	Mean	SD
Age (years)	160	29.89	1.93	80	29.84	2.14	80	29.93	1.70
Any schooling	160	0.27	0.17	80	0.28	0.18	80	0.26	0.16
Married	160	0.98	0.03	80	0.99	0.03	80	0.98	0.04
Age married (years)	160	17.50	0.74	80	17.49	0.73	80	17.51	0.75
No. sons	160	1.60	0.33	80	1.61	0.34	80	1.58	0.32
No. daughters	160	1.65	0.34	80	1.59	0.36	80	1.70	0.31
Hindu religion	160	0.72	0.15	80	0.74	0.17	80	0.71	0.14
Worked in past 7 d	160	0.59	0.19	80	0.60	0.19	80	0.58	0.18
Worked in past 12 mo	160	0.95	0.07	80	0.94	0.08	80	0.96	0.06
Paid cash for work	160	0.09	0.10	80	0.09	0.10	80	0.09	0.09
Days childcare prevents work	160	1.60	1.67	80	1.78	1.88	80	1.41	1.42
Below poverty line	160	0.51	0.18	80	0.52	0.19	80	0.50	0.17

^a^ Variables are: age in years (age); whether the respondent ever attended school (any schooling) or not; whether the respondent was married (married) or not married, including widowed, divorced, separated, or living together married; the age at marriage, if married (age married); the number of sons under age 18 y who live at home (no. sons); the number of daughters under age 18 y who live at home (no. daughters); Hindu religion (Hindu) or other, including other religion, no religion, or unknown; whether the respondent worked in the past seven days (worked in past 7 d) or not; whether the respondent worked in the past 12 months (worked in past 12 mo) or not; whether respondents who reported working in the past 12 months were paid in cash (paid cash for work) or not; the number of days in the past month that respondents who reported working in the past year were unable to work because of childcare (days childcare prevents work); and whether the household has a Below the Poverty Line card (below poverty line)

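### Schooling is recorded only for children under 18 in the household; if that rule is reused at follow-up, girls who marry or leave home drop out of a primary outcome, and daycare may change how many do

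*Protocol article*

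**What the plan says.** The Methods paragraph of the abstract names the primary social and economic outcomes as "women’s economic status and economic opportunity, women’s empowerment, and children’s educational attainment". Schooling is next described under Other covariates, where the mother reports "literacy, enrollment in school, time spent in school in the prior year, highest level of education completed", and does so "for all children in the household who were less than eighteen years of age". No other rule says which children contribute to the outcome. The footnote to Table 1 uses the same frame for a baseline descriptor: "the number of daughters under age 18 y who live at home".

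The Background explains where a schooling effect is expected: "The demand of caring for younger siblings is a key explanation for why adolescent girls, on average, dropout from school before boys". It adds that this limits women's opportunities "indirectly by hastening marriage and the time to first childbirth".

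Mothers are to be re-interviewed in early 2016 and early 2017. The attrition paragraph in the Discussion deals with the loss of respondents, who are the mothers. It does not mention children leaving the household.

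**The concern.** Whether a daughter still lives at home at follow-up is settled after randomization. On the article's own account, marriage lies downstream of sibling care and dropout, which daycare is meant to relieve. If the outcome exists only for girls still in the household, the arms are compared within a group that the intervention may have helped to select.

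The planned safeguards do not reach this. Keeping the mother in the study does not keep her married daughter in the outcome. Intention-to-treat analysis and adjustment for pre-treatment values cannot supply a follow-up value that was never asked for. At stake is the reading of a primary outcome in adolescent girls, the group in which the Background expects the effect.

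**Working it through.** **Plan's own figure.** The article gives no power or departure figure for schooling. Its only sample size result is a detectable difference of 5 to 7 points in labor force participation. With 160 clusters of 20, variance 0.21, P = 0.5, and two-sided 5% assumed, (0.8416 + 1.9600) × 2 × √(0.21 × (1 + 19 × ICC)/3200) gives 4.95 points at ICC 0.01 and 6.34 at 0.05. That is consistent with the article and has no bearing here.

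**What the distortion depends on.** In each arm let m be the share of the baseline roster that has left home, s the proportion enrolled among those still at home, and l the proportion enrolled among leavers. Enrollment in the fixed roster is (1 − m)s + ml = s − m(s − l); the in-household rule shows s. So, with 1 for treated and 0 for control:

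observed difference − fixed-roster difference = m₁(s₁ − l₁) − m₀(s₀ − l₀).

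This is zero when departure and the schooling gap between leavers and stayers are the same in both arms. Otherwise its sign depends on which product is larger. The article gives none of m, s or l for daughters.

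**Illustration (all inputs assumed).** Girls who would stay home in either arm: 60% enrolled. Girls who have left: 0% enrolled. Girls kept home only because of daycare: enrolled as shown. No effect on girls who would stay anyway.

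| Leave, control / treated | Enrolled if kept home | Fixed roster, control / treated | True difference | In household, control / treated | Observed difference |
|---|---|---|---|---|---|
| 20% / 10% | 20% | 0.80 × 0.60 = 48.0% / 48.0 + 0.10 × 20 = 50.0% | +2.0 | 60.0% / 50.0/0.90 = 55.6% | −4.4 |
| 10% / 5% | 20% | 0.90 × 0.60 = 54.0% / 54.0 + 0.05 × 20 = 55.0% | +1.0 | 60.0% / 55.0/0.95 = 57.9% | −2.1 |
| 20% / 10% | 60% | 48.0% / 48.0 + 0.10 × 60 = 54.0% | +6.0 | 60.0% / 54.0/0.90 = 60.0% | 0.0 |
| 20% / 20% | none kept home | 48.0% / 48.0% | 0.0 | 60.0% / 60.0% | 0.0 |

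**Is marriage before 18 plausible?** Table 1 gives the respondents' age at marriage as mean 17.47, SD 2.85. With a normal approximation, Φ((18 − 17.47)/2.85) = Φ(0.186) = 0.574, so about 57% of the mothers married before 18. This shows only that marriage can fall within the roster's age range, if daughters resemble their mothers.

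**Turning 18.** A child aged 16 or 17 in early 2015 is 18 or older by early 2017. Date of birth is fixed before randomization, so this loss does not by itself separate the arms. As a rough size, a simulation with normal approximations to the mothers' age (29.87, SD 6.86) and age at marriage, and a first birth assumed 1 to 3 years after marriage, puts about 7% to 9% of mothers with an oldest child of either sex aged 16–17 at baseline, and about 16% to 19% with one aged 14–17.

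**The case against.** The strongest reply is that the article states no end-line rule. The sentence on schooling is in the past tense, only the baseline had been fielded, and the mid-line survey was still being planned. Follow-up rosters are detail that an article may leave to the questionnaire or the full protocol, and adjusting for pre-treatment values is at least compatible with following the baseline children.

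Part of this stands: reuse of the rule at follow-up is an inference. But the tense does not confine the rule to baseline. Outcome measures describes time use, employment, and child height and weight in the past tense too, and these are clearly meant to be measured again. The article does fix a roster rule and does discuss attrition, yet that discussion passes over an exit that its own model predicts. Nor can a later analysis plan recover the schooling of a daughter about whom nobody asked.

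A second reply is that the main hypothesised route is direct: relief from sibling care keeps girls in school while they live at home. Gains among girls who stay would be visible under the in-household rule, and time from the start of daycare in fall 2015 to early 2017 is short for marriage to shift much. This also stands. The illustration leaves out any direct gain, so it shows a mechanism and not an expected result. The affected girls may be a minority of the children.

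**Conclusion.** The point holds conditionally. A primary outcome rests on a roster rule that, if reused at follow-up, would condition schooling on household membership after randomization, and the article's own mechanism gives a reason for membership to differ by arm. Size and direction cannot be computed from the article. The assumed scenarios run from no distortion to a change of sign.

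A reader might infer more than the article supports:

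- That turning 18 is part of the bias. It is not: it is balanced by randomization, and only narrows the estimand and costs precision.
- That the 57% measures the loss. It is the cumulative share of the mothers' generation married before 18, whereas the distortion depends on departures of daughters, by arm, over the follow-up.
- That the bias must run toward no effect. This follows only from chosen inputs. If departure were similar in both arms and daycare raised schooling among girls at home but not among leavers, the in-household difference would exceed the fixed-roster one.
- That the loss is certain. No rule specific to the follow-up surveys is stated.

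**What to change.** At both follow-ups, pre-load the baseline roster and ask the mother the same schooling questions, plus residence and marital status, for every child listed under 18 at baseline, whatever the child's present age or residence. Define the educational outcome in that fixed roster, and describe children new to the household separately. Report departures from the household by arm, with marriage shown separately.

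The same mother is already being interviewed and the mid-line survey was still in planning at submission, so the cost is a roster pre-load and a few extra questions. The downside is some proxy reporting for children who have left home. No sample size figure changes.

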### Statistical analyses

Descriptive statistics, including comparisons of means and proportions, were used to compare socio-demographic characteristics between the treatment and control arms (Table 1). We will conduct intention-to-treat analyses assuming that respondents complied with their initial treatment assignments. We will estimate the impact of the treatment, access to affordable daycare, on primary endpoints with marginal linear and log-linear regression models using generalize estimating equations to account for clustering at the hamlet level [34]. Multivariable regression will be used to control for block, which was used to stratify the randomization, and pre-treatment values of endpoints, in order to improve the precision of our estimates. Results will be reported on the absolute and relative scales as risk differences and risk ratios with their respective 95 % confidence intervals. Results will be reported following the CONSORT statements for randomized trials and cluster randomized trials [35, 36].

### Trial status

At the time of submission the intervention had been introduced in treatment areas and data collection as part of the mid-line survey was being planned.

## Discussion

This paper provides the protocol for a cluster-randomized evaluation of the impact of access to affordable daycare on social, economic, and health outcomes of rural Indian women and their children. Prior evidence of daycare impacts on women has been limited by non-randomized designs, and outcomes have generally focused on children rather than mothers. Moreover, most prior research has been conducted in Latin America.

We are monitoring and attempting to mitigate threats to the internal validity of our study, which include partial compliance, attrition, and spillovers. First, partial compliance could occur if hamlets assigned to the treatment arm did not open a daycare center or closed a daycare center before the end of the study period; this would tend to reduce the difference in treatment receipt between treated and control clusters and dilute the true treatment effect. A daycare center might close in a treated hamlet if a government anganwadi were to open in the same hamlet (Seva Mandir does not operate balwadis in hamlets with a government anganwadi). Additionally, a center might close if a sanchalika became unable to operate the center and a suitable replacement could not be identified. Seva Mandir has worked in partnership with the community in the Udaipur District since 1968 and study hamlets were restricted to areas with adequate demand expressed by village councils; thus, we do not anticipate substantial non-compliance in our treatment arm. Treatment effects might also be diluted if government anganwadis are established in control hamlets. Second, attrition could occur in our study if respondents are lost to follow-up during the study period. We are attempting to prevent selection bias by minimizing losses to follow-up; strategies include making at least three visits to respondents’ homes to conduct interviews, collecting detailed address and telephone information to track individuals over time for follow-up interviews, and providing an incentive to participate in the study. Given the relatively short time frame for our study we do not expect a substantial rate of attrition. Third, spillovers could occur if, for example, respondents of control villages enrolled their children in balwadis in treatment villages. In order to reduce potential spillovers, we utilized a cluster-level design and did not select control hamlets within a buffer of approximately 1.5 kilometers from a treated hamlet. Moreover, hamlets in the region are typically dispersed and daily travel between hamlets is relatively rare. Seva Mandir’s prior work suggests that the risk of women in a neighboring hamlet taking up day-care in a treated hamlet is low.

Rajasthan is among India’s poorer states and the results of our study may better generalize to other low-income contexts. However, there may be limitations to our study in terms of external validity and potential scale-up. Our study is being conducted in selected areas that have adequate demand to sustain a daycare center. Additionally, we are evaluating a model of daycare designed by a non-governmental organization that has been operating in the region for many years. Whether results concerning the impact of the balwadi program can be generalized to other rural areas lacking affordable daycare service within India, or to different daycare models, is unclear.

Caveats considered, there are several strengths to our study. First, randomization provides rigorous evaluation by ensuring that treatment and control groups are similar with respect to measured and unmeasured characteristics. Second, randomization at the hamlet-level limits the potential for spillover or contamination effects. Third, the extent to which the costs of day-care programs are offset by benefits is unknown and we will perform a prospective cost-effectiveness analysis to increase the policy relevance of our findings.

Cost-effective interventions to improve women’s empowerment are urgently needed, especially in regions where existing indicators suggest that women’s empowerment is low. Our cluster-level design, described in this study protocol, will help to improve the quality of evidence on whether providing community-run full-time daycare may improve economic opportunities and empowerment among rural women.

